### Study measures

All study measures will be completed at the site of the interdisciplinary service at baseline. However, people who are unable to attend the clinic for a follow-up assessment will be posted self-report questionnaires. Questionnaires will be self-administered except in cases where it is clear that the patient is unable to complete the questionnaire due to an impairment (such as visual disturbance) that makes self-completion difficult. In these cases questionnaires will be interviewer-administered. Table 1 provides a summary of each of the measures at each time point.

**Table 1 T1:** Study outcome measures at each follow-up time

**Baseline**	**3 months**	**6 months**	**12 months**
SF-36	SF-36	SF-36	SF-36
BMI and waist measurement	BMI and waist measurement	BMI and waist measurement	BMI and waist measurement
Comorbiditymeasure	Comorbidity measure	Comorbidity measure	Comorbidity measure
K6			
Medical Outcomes Study Social Support Survey			
TUG	TUG	TUG	TUG
Self-reported health perception question	Self-reported health perception question	Self-reported health perception question	Self-reported health perception question
Sociodemographic information			
	Intervention data	Intervention data	Intervention data

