### Study design

A longitudinal cohort study focusing on the health outcomes and costs of patients with chronic diseases attending the service will be implemented. Patients will be evaluated at baseline (intake to the service), and at 3-, 6-, and 12-months after intake to the service. The 3- and 6-month follow-ups were included to evaluate short-term outcomes after commencement of the intervention. The 12-month follow-up was included to evaluate intermediate outcomes to pick up a potential delay in the positive impact of intervention on some dimensions of health. This study has been prospectively registered with the Australian and New Zealand Clinical Trials Registry (ACTRN12611000724976).

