### Study objectives

#### ***Aims***

1. To examine the effectiveness of the service up to 12-months post-intake in improving a range of health outcomes (including length of stay in hospital, number of admissions, health state, preference based health state, and health-related costs).

2. To examine the effect of a range of factors including comorbidities, sociodemographic factors, and type of intervention received, on the health state, preference-based health state, length of stay in hospital, number of admissions, and health-related costs of people attending the service up to 12-months post intake.

3. To determine the difference in health between clients attending the service before and after receiving intervention and the general population using Australian population normative data.

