### Participants and selection criteria

All clients who attended the service will be eligible to participate. The following are inclusion criteria: presence of at least one chronic disease; aged 18 or older; and attendance at their first intake appointment. In addition, clients will be required to attend a minimum of one intervention session at the service for follow-up data to be included in analyses of clinic effectiveness over time. The following are exclusion criteria: a severe communication disability or behavioural disorder that would compromise the ability to participate in the intervention program or complete the questionnaires; a cognitive deficit that impairs the ability to read and write; and known pregnancy or up to 6-months postpartum that would influence body mass index (BMI), waist measurements, and possibly other outcomes. All participants receive individually tailored care prescribed by the service.

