Adjustment will made for wave missing data (where a subject misses an entire visit) using inverse probability weighting [38]. This is a two-stage procedure. In the first stage a logistic regression model is used to predict which subjects are more likely to be missing at each follow-up time. This model will include time, demographic factors and comorbidity factors collected at baseline. The probability of each subject being missing at each time is then calculated and inverted to create a weight that can be used in the regression models described above. As an example, if men at 12-months have a 0.5 probability of responding, then the weight for men is 2 so that the results for those men who responded at 12-months are doubled. This will enable a sensitivity analysis with comparison to the complete case analysis to be conducted.

The health of the study sample (using SF-36 scores) will be compared to Australian normative data [39] matched on select sociodemographic variables such as age, gender and select chronic diseases using unpaired t-tests with 95% confidence intervals.

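### The postal questionnaire is tied to being unable to attend, so clients who could attend but do not return have no stated route to give follow-up SF-36 data

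*Protocol article*

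**What the plan says.** All references are to the Protocol article.

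- **Collection (Study measures).** Baseline measures are completed at the clinic. For follow-up, "people who are unable to attend the clinic for a follow-up assessment will be posted self-report questionnaires". The term for inability is not defined. A separate rule covers how forms are completed: "Questionnaires will be self-administered except in cases where it is clear that the patient is unable to complete the questionnaire due to an impairment"; such clients are interviewed instead.
- **Timing (Study design).** "Patients will be evaluated at baseline (intake to the service), and at 3-, 6-, and 12-months after intake to the service". The clock runs from intake and does not depend on whether care continues.
- **Who counts (Participants and selection criteria).** "clients will be required to attend a minimum of one intervention session at the service for follow-up data to be included" in the effectiveness analyses. Nothing further is required, so a client who stops after one session stays in scope.
- **Question (Aims, item 1).** "To examine the effectiveness of the service up to 12-months post-intake in improving a range of health outcomes".
- **Missed visits (Data analysis).** Inverse probability weighting is planned for whole missed visits, with weights from a logistic model. "This model will include time, demographic factors and comorbidity factors collected at baseline". On its role: "This will enable a sensitivity analysis with comparison to the complete case analysis to be conducted".

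**The concern.** The analysis population includes clients who have stopped or finished care, but the stated fallback for collecting their scores depends on a reason for absence that many of them will not have. A client who is well enough to travel and simply sees no reason to return does not meet the stated trigger.

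If the rule is applied as written, having a follow-up SF-36 depends partly on still being engaged with the clinic. Engagement is plausibly related to how health has changed. This is a one-group before-and-after comparison, so there is no second arm in which similar non-response might cancel. The expected effect is small (Hypotheses, item 1: effect size at most 0.2), so a modest selection effect can matter for whether health is read as maintained, improved or declining.

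**Working it through.** **Step 1. Set the rules side by side.**

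| Client at a follow-up date | Due for assessment? | In the effectiveness analysis? | Stated route for SF-36 |
|---|---|---|---|
| Attends the clinic | Yes | Yes, after one session | Clinic |
| Cannot attend | Yes | Yes, after one session | Post |
| Could attend, does not return | Yes | Yes, after one session | None stated |

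The third row is the gap.

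**Step 2. Ask whether the planned weighting closes it.** Weighting removes the bias only if, given the variables in the missingness model, response is unrelated to outcome. The listed variables are time, baseline demographics and baseline comorbidity. Neither engagement nor baseline SF-36 is listed. If no non-returner responded, even a model that included engagement would have no responders of that kind to weight up. Collection therefore has to be repaired first.

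**Step 3. Find a yardstick.** The protocol gives no response rate and no outcome by engagement, so it has no figure of its own for this bias. Its nearest figures are in Sample size and power: 130 participants, a 5-point difference, 80% power, two-sided 5%, and an important difference of 3 to 5 points. The standard deviation (SD) of change is not stated, so 130 cannot be reproduced from stated inputs. Solving n = ((1.96 + 0.84) × SD / 5)² for n = 130 gives an SD of about 20.3. An assumed SD of 20 gives 126 (normal) or 128 (t). With 20.3, the standard error of a mean change in 130 clients is 20.3 / √130 ≈ 1.8 points.

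**Step 4. Illustrate the bias. All inputs here are assumed.** Let f be the share of non-returners, r their response rate, 0.9 the response rate of everyone else, and D the difference in mean SF-36 change (others minus non-returners).

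- Share of non-returners among responders: w = f·r / (f·r + (1 − f)·0.9)
- Bias in the observed mean change: (f − w)·D

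With r = 0, w = 0 and the bias is f·D: 0.2 × 2 = 0.4 and 0.4 × 5 = 2.0. With r = 0.3 and f = 0.4, w = 0.12 / (0.12 + 0.54) = 0.182, so for D = 5 the bias is 0.218 × 5 = 1.09.

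| f | D | r = 0 | r = 0.3 | r = 0.6 |
|---|---|---|---|---|
| 0.2 | 2 | 0.4 | 0.25 | 0.11 |
| 0.2 | 5 | 1.0 | 0.62 | 0.29 |
| 0.4 | 2 | 0.8 | 0.44 | 0.18 |
| 0.4 | 5 | 2.0 | 1.09 | 0.46 |

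These are SF-36 points. A positive D (non-returners do worse) overstates the mean change. A negative D of the same size understates it by the same amount. With D = 0 there is no bias.

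**Step 5. Scale it.** With no response from non-returners, 0.4 to 2.0 points is 8% to 40% of the 5-point target (0.4/5 and 2.0/5). If 60% of them respond anyway, it falls to about 0.1 to 0.5 points.

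**The case against.** The strongest reply is that the text does not restrict posting to those who cannot attend. It does not say what happens to others, and inability may be loose shorthand for anyone who does not come in. A condensed article may also leave reminders and tracing to a fuller document. This stands as far as it goes: that able non-returners are denied a questionnaire is an inference, not something the protocol says. What remains is that the article does state a trigger, and that trigger, followed literally, does not reach a group kept in the 12-month question.

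A second reply is that the analysis already mitigates the problem. Baseline SF-36 is a predictor in the outcome models, and length and type of intervention are candidate predictors (Data analysis). This helps in part. However, the lasso may drop the intervention variables, and a client with no follow-up score contributes no SF-36 outcome.

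Two stronger readings are tempting and are not supported:

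- **That the bias favours the service.** Clients who left because the programme did not help would push the estimate up if lost, but clients who finished successfully and saw no need to return would push it down. The documents give no outcomes, response rates or discharge times by engagement.
- **That the posting and interviewer rules contradict each other for an impaired client who cannot attend.** The interviewer exception is not limited to baseline or to the clinic. It follows directly after the posting sentence and naturally overrides it.

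**Conclusion.** The point holds in a limited form. The stated trigger for posting is narrower than the population that Aim 1 needs, and the listed missingness predictors do not include engagement or baseline SF-36. Follow-up SF-36 data may therefore depend on engagement in a way the planned weighting does not address.

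The direction is open. The size is about 0.4 to 2.0 points either way if 20 to 40% of clients are non-returners, their mean change differs by 2 to 5 points and none respond. It is less if some do, and nil if their outcomes do not differ. None of these inputs comes from the protocol.

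The effect is confined to outcomes collected from clients at follow-up. Hospital days, admissions and Medicare-based costs come from records (Health outcomes; Healthcare costs) and are not touched. No figure in the protocol is shown to be wrong. This is an inexpensive improvement to a collection rule, worth making because the design has one group and expects a small effect.

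**What to change.** 1. **Change the trigger.** Post the self-report questionnaires to every client who has not completed a clinic follow-up within a set window of the 3-, 6- or 12-month date, whatever the reason and whether or not still in care, unless consent to follow-up is withdrawn. The existing interviewer exception continues to apply. If the present wording was already meant this way, a one-line clarification is enough.
2. **Record** the reason for non-attendance and the mode of completion, so that differences by mode can be examined.
3. **Extend the missingness model** with sessions attended and baseline SF-36. Baseline SF-36 is already collected. Attendance should be available from the intervention data and is needed anyway to apply the one-session rule. Take it from service records, so that it exists for clients who do not return.

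Cost: some postage and staff time, and more SF-36 scores completed by post instead of in the clinic. The postal process is already planned, so this widens its use and adds no new procedure.

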### Health outcomes

Health will be measured using the Australian SF-36 (Version 1). The SF-36 is a 36-item generic measure of health with eight scales including physical functioning, role limitations, bodily pain, social functioning, general mental health, role limitations, vitality, and general health perceptions [9]. Two summary scores are obtained from these scales: a physical components summary and mental components summary. Extensive psychometric testing has occurred using people with a wide range of chronic diseases or single chronic diseases [10-13]. A review of studies has demonstrated that the SF-36 is superior in terms of sensitivity to change and responsiveness compared to other measures of health [9]. In addition, the SF-36 has been shown to discriminate between types and severities of chronic diseases and to distinguish between people with a chronic medical condition only, from those with a chronic medical condition plus a psychiatric disorder [14]. A preference-based measure of health will be derived from the SF-36 to produce a summary health score (multi-attribute utility score) for individuals at each time point.

Hospital utilisation will be measured using the number of days spent in hospital and number of hospital admissions during the one-year follow-up as indicators for intervention effectiveness. This will be accessed from hospital records for each participant.

### Healthcare costs

Healthcare costs will be determined using Medicare and hospital utilisation records. Medicare data (including Pharmaceutical Benefits Scheme data) will be accessed for the 12-months prior and 12-months following intake (baseline), which will permit estimation of within-patient change in healthcare costs. This data will allow costing of Hospital, Medicare and Pharmaceutical Benefits Scheme related items that will include inpatient admission costs, out-of-pocket expenses for general practitioners and specialist medical appointments, and out-of-pocket medication related expenses. Clinic health professional labour costs related to delivering the interdisciplinary intervention to study participants will also be recorded. Expenses related to alternative medications will not be captured by these data sources.

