## Methods

### Setting and services

The regional interdisciplinary chronic disease health service is located in a regional city (Rockhampton) approximately 700 kilometres from the state’s capital. Services are provided to people with chronic diseases in the regional city and surrounding rural and remote areas (providing services to more than 100,000 residents). Referral to the interdisciplinary clinic can arise from three sources: self referral, referral from the local hospital or referral from a general medical practitioner; although the majority (90%) are referred by their general practitioner [1]. Services are delivered by an interdisciplinary team of nurses and allied health professionals, including podiatrists, occupational therapists, exercise physiologists, a social worker, a speech pathologist, a dietician, a physiotherapist, a pharmacist and an indigenous health worker. Qualified professional supervisors in allied health disciplines supervise up to four students each who provide a range of services to clients with a wide range of chronic diseases that include hypertension, osteoarthritis, high cholesterol, diabetes, and chronic back pain. The process for obtaining services is shown in Figure 1.

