#### ***Hypotheses***

1. Health will be maintained or improve over time from intake (baseline) to 12-months after intake with a small average effect size anticipated for improvement (effect size ≤ 0.2).

2. Health outcomes will be moderately to strongly and negatively associated with the number of chronic diseases (effect size ≥ 0.5).

3. Days in hospital and inpatient admission costs will decrease after intake to the service compared with before intake to the service.

4. The health of clients attending the service will be worse than the general population using Australian population normative data at all times (effect size ≥ 0.2).

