### Sample size and power

A minimum sample size of 130 participants is required to examine the change over time from baseline to 12-months post-intake of the SF-36; using a one-group longitudinal design, a power of 80% with a two-sided type 1 error of 5% to detect a difference of at least 5 points in the social functioning scale of the SF-36 using a t-test [33]. Three to five points of change in SF-36 scores has been reported as the minimally clinically important difference [33,34] and is equivalent to a small effect size for those with chronic diseases [34]. A small effect size is anticipated for changes in health over 12-months based on the small to large effect sizes found in treatment effectiveness studies using the SF-36 in related chronic disease studies over similar times [7,12,34,35] and the high percentage of clients with multiple chronic diseases attending the service prior to the study commencement, for whom moderate to large effect sizes are unlikely. The sample size calculation was based on the social functioning scale of the SF-36 as this outcome would likely show the smallest difference and therefore need the largest sample size. Therefore, provided the study sample size exceeds 130 participants, this investigation should have greater than 80% power for all outcomes.

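### The before-after contrast of cost and hospital use includes the months in which clients were referred, so it can show a fall with no service effect.

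*Protocol article*

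**What the plan says.** - Hypotheses, item 3: "Days in hospital and inpatient admission costs will decrease after intake to the service compared with before intake to the service". No length is given for the period before intake.
- Healthcare costs: of the Medicare records, which cover the Pharmaceutical Benefits Scheme, the article says that they "will be accessed for the 12-months prior and 12-months following intake (baseline), which will permit estimation of within-patient change in healthcare costs". On the cost items: "This data will allow costing of Hospital, Medicare and Pharmaceutical Benefits Scheme related items that will include inpatient admission costs".
- Health outcomes: hospital use is taken from hospital records as the "number of days spent in hospital and number of hospital admissions during the one-year follow-up as indicators for intervention effectiveness". No pre-intake window is given here.
- Setting and services: clients arrive by "self referral, referral from the local hospital or referral from a general medical practitioner", and 90% come from their general practitioner.
- Sample size and power describes a one-group longitudinal design. No comparator appears anywhere in the article.
- Data analysis: the SF-36 models use the baseline score as a predictor, partly to help with regression to the mean. Cost, hospital days and number of hospitalisations use the same model with a Poisson distribution.

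The article describes no gap before intake, no look-back longer than 12 months and no pre-intake trend.

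**The concern.** Intake is not a random date in a client's life. Most clients get there because someone in the health system referred them, and that contact may have followed an admission, an exacerbation or a run of appointments. Such care lies before intake, often shortly before, and nothing matches it after intake. With a single group, a before-after contrast cannot tell the passing of that episode from a benefit of the service.

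The stakes are Hypothesis 3 and the hospital-use and cost parts of Aim 1. The article calls hospital use an indicator of effectiveness, and its Discussion expects the economic results to inform other services considering a similar model. A larger sample would only narrow the interval around a biased value.

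**Working it through.** **The plan's own figures.** The article gives no expected rate, effect or sample size for hospital use or cost, so there is nothing on this point to reproduce. Its sample size of 130 concerns a 5-point change in SF-36 social functioning. It is used below only as a study size.

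**Inputs from the article.** One group; 12 months before and 12 months after intake for Medicare and pharmaceutical data; 90% general-practitioner referral. Self and hospital referral together are therefore 100% - 90% = 10%, which is the ceiling for direct hospital referral.

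**Assumed inputs (not in the article).** A share q of 5% or 10% of clients has one extra admission that led to referral; that admission lasts 5 days; the background rate r is 1, 2 or 4 hospital days per client-year, equal in both years; the service has no effect.

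**Hospital days.** Expected days before = r + 5q; expected days after = r. Apparent fall = 5q / (r + 5q).

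| r (days/year) | q = 5% (excess 0.25 day) | q = 10% (excess 0.50 day) |
|---|---|---|
| 1 | 0.25/1.25 = 20% | 0.50/1.50 = 33% |
| 2 | 0.25/2.25 = 11% | 0.50/2.50 = 20% |
| 4 | 0.25/4.25 = 6% | 0.50/4.50 = 11% |

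If q = 0, the fall is zero.

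**Number of admissions.** With a background rate λ of 0.3, 0.5 or 1.0 admissions per client-year (assumed), the apparent fall is q / (λ + q). How often a study of 130 would declare a significant fall was simulated: 4000 runs, client rates gamma-distributed with shape 1, no service effect, two-sided 5% test. A paired t-test and a Poisson comparison of totals agreed to within about one percentage point. The nominal rate of false falls is 2.5%.

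| λ | q = 5%: fall; significant fall | q = 10%: fall; significant fall |
|---|---|---|
| 0.3 | 14%; about 12% | 25%; about 28-29% |
| 0.5 | 9%; about 7% | 17%; about 18% |
| 1.0 | 5%; about 6% | 9%; about 11% |

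At q = 0 the simulated rate was 2.2-2.9%, as it should be.

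**Does baseline adjustment help?** Suppose the step in Data analysis is carried over in full, with pre-intake use as a covariate for cost, days and admissions. It then helps to explain differences between clients in later use. It does not say what the group's mean use would have been without the service, so the mean fall keeps its spurious part.

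**What offsets it.** At q = 10%, a rise of 0.5 day per client in the year after intake, for instance from worsening disease, would cancel the excess exactly. At q = 5%, 0.25 day would.

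**Effect of omitting the run-up.** If the triggering admissions fall in the last 3 months before intake, months -12 to -4 carry 9/12 of r, and so do the first 9 months after intake. At r = 2 that is 1.5 days on each side and no fall. Each of these months is paired with the same calendar month a year later, so season stays matched.

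**The case against.** Several counter-arguments have force.

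- **The window for hospital use is not stated.** The 12-month look-back is explicit only for Medicare and pharmaceutical data. For hospital days and admissions, Health outcomes gives the follow-up year alone. A reader might infer that the article fixes a 12-month pre-intake year for hospital use; it does not. Hypothesis 3 still needs some pre-intake hospital period, and inpatient cost is named within the cost outcome. This objection stands, and it is a reason to state the window.
- **Nothing shows that admissions led to referral.** General practitioners refer 90% of clients, the conditions listed include hypertension, osteoarthritis and high cholesterol, and a hospital referral need not follow an inpatient stay. A reader might infer that triggering admissions load the pre-intake year by the very design; the documents show only that they can. This stands as a limit on size. It does not remove the mechanism, since a general practitioner may refer after a discharge, and the appointments and medicines around a referral count towards cost.
- **The net direction is not fixed.** A reader might infer that the bias must always favour the service. This mechanism does, but the Discussion refers to conditions likely to worsen whatever the intervention, and clinic labour costs, if counted in the total, arise only after intake. This stands.
- **The claims are modest, and regression to the mean is recognised.** The article calls its evidence preliminary and a platform for later trials. That tempers the consequences, but effectiveness is still Aim 1. The regression-to-the-mean step does not isolate the mean fall, as shown above.
- **A sensitivity analysis may be left to a fuller document.** That is fair for details. The full-year cost contrast, however, is stated in the article, with nothing to limit how a fall will be read.

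**Conclusion.** The concern holds as a possible bias of unknown size. The cost contrast sets the full 12 months up to intake against the 12 months after in one group that enters largely by referral, and Hypothesis 3 predicts a fall on the same before-after basis. A fall can therefore appear with no service effect, and the planned baseline adjustment does not remove it.

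Under the assumptions given, the spurious fall in hospital days is about 6-33%. It tends to zero when few clients had a triggering admission, and it could exceed the range shown for a given background rate if general-practitioner referrals often follow discharge. These figures illustrate the mechanism; they do not show that it operated in this clinic. Worsening disease could reduce or reverse the net change. The point merits an inexpensive addition to the analysis and a limit on attribution. It does not require replacing the full-year contrast.

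**What to change.** 1. State the pre-intake window for hospital days, admissions and inpatient costs, matching the 12 months given for Medicare and pharmaceutical data.
2. Keep the 12-versus-12-month contrast. Pre-specify beside it a contrast that omits the 3 months before intake: months -12 to -4 against the first 9 months after intake. The 3-month gap is a judgement, and the quarterly series in item 3 helps to check it.
3. Show hospital use and cost by quarter around intake, and give results by referral source.
4. State that a fall seen only in the full-year contrast will not be attributed to the service.

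Cost: a little more analysis. The added contrast has wider intervals and leaves out months 10-12, when a delayed benefit might show, which is one reason to keep the full-year contrast. The figure may be less favourable to the service. Dated pre-intake hospital records must be obtained if they have not already been requested.
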